### 1. INTRODUCTION

#### a. Background

Leprosy is a chronic infection that caused by *Mycobacterium leprae* (*M. leprae*) which attacked skin, peripheral nerve, upper airway mucosa, and eye. *M. leprae* is an obligate intracellular acid-fast bacillus (AFB), rod-shaped, and multiply inside histiocytes, Schwann cells, muscle cells, and vascular endothelia. Leprosy can be transmitted through skin-to-skin direct contact in the long term. Factors that influence the spread of leprosy are: *M. leprae* pathogenesis, mode of transmission, immunology status, individual genetics, socio-economy status and environmental factor (Wisnu, *et al.* 2016; Fitness, Tosh & Hill 2002).

According to World Health Organization (WHO), leprosy can be divided into 2 types, paucibacillary (PB) and multibacillary (MB). Ridley and Jopling classified leprosy into several zones of a spectrum, which are TT (polar tuberculoid), BT (borderline tuberculoid), BB (mid-borderline), BL (borderline lepromatous), LL (polar lepromatous). MB type includes LL, BL, and BB types, whereas PB type include TT and BT types (Wisnu, *et al.* 2016)

Leprosy prevalence universally in the end of 2014 is 175.554 and the number of new cases is 213.899 (WHO 2016b; Kemenkes 2016b; WHO 2016a). Leprosy endemically found in developing countries in the tropic and subtropic areas, such as Asia, Africa, and Latin America because limited access to health facility, education, and lower social and economic

welfare. Southeast Asia is a developing countries region with the highest number of new leprosy cases in the world of 154.834 cases in 2014. Indonesia is one of the developing countries with highest new leprosy case amount in Southeast Asia and the third highest in the world after India and Brazil (Hogeweg 2010; WHO 2016a). In 2015, there was 17.202 new leprosy case in Indonesia with 84.5% of it are MB typed. Until recently, leprosy is still one of the health problems in Indonesia. Even though leprosy has been eliminated in 2000, leprosy cases in Indonesia is still relatively static (Kemenkes 2016b).

Leprosy is a systemic infection with ocular complication leading to visual impairment that could end in blindness (Rahinam 2010). Most ocular complication was found in elderly patient with MB type leprosy (Hogeweg 2010; Courtright & Lewallen 2006; Lewallen & Courtright 2012). About 70-75% of leprosy patients in the world experienced ocular complication, with 10-50% in severe condition and 5% end in blindness (Grzybowski, et al 2015). Blindness can be caused by several factors, such as leprosy type, duration, medication effect, and eye disorder management. There was not much data available regarding leprosy, although a survey estimated 25-50% of the population of leprosy patients or who have recovered from leprosy have eye disorders (Courtright et al 2002). WHO divided eye disorders in leprosy into 2 grades, according to visual acuity (VA): grade 1 with  $VA \geq 6/60$  and grade 2 with  $VA < 6/60$  (Ebenezer 2016).

Courtright et al (2002) in India, Phillipines, and Ethiopia found that 11% of MT type leprosy patients have eye disorders which potentially lead to blindness, and 2,8% of them will be blind (Courtright et al. 2002). Study done by Singh et al (2014) showed eye disorders were found in 39,4% leprosy patients with 13,07% grade 1 visual impairment and 19,86% grade 2 visual impairment (Singh et al. 2014). Another study by Rao (2015) showed the most common eye disorders are madarosis (58,33%), corneal involvement (38,8%), lagophthalmos (28,89%), while blindness found in 30,55% patients (Rao 2015).

Data regarding eye involvement in leprosy patients in Indonesia have not been published much. A survey in rural area of Gresik and Lamongan, East Java, in 1997-1998 showed that there were eye disorders in 7% out of 112 leprosy patients with disability (Schreuder et al 2002). A study done in Cirebon in 2010-2011 showed that grade 2 visual impairment were found in 5,6% of the new leprosy cases (Peters et al. 2013). Another study by Arifin R from March 2016 to May 2017 in Tangerang showed from 138 MB type leprosy patients, 25 patients had uveitis and 11 patients of them (44%) had bilateral uveitis. In this study, uveitis found mostly in men (80%), MB type LL leprosy (64%), age 60 years old, and duration of leprosy 42 years (Arifin 2017).

Clinical manifestations of eye disorders in leprosy were divided into adnexal/extraocular and intraocular manifestations. Eye disorders pathogenesis in leprosy divided into tuberculoid (TT) and lepromatous (LL) types. Eye disorder in TT type leprosy mostly happened in adnexal area, including eyelid, mainly if there was a focal lesion above facial cranial nerve (CN VII) that innervates orbicularis oculi muscle. This process usually happened unilaterally and rarely leading to intraocular manifestations. LL type process happened more slowly, more symmetric than TT type and more commonly leads to intraocular manifestations. LL type patients have higher risk in ocular complications (Grzybowski, et al. 2015; Ebenezer 2016; Sjamsoe & Sjamsoe-Daili 2003).

Orbicularis oculi muscle works to close eyelid and innervated by CN VII. Lagophthalmos and disturbance in tear excretion could happened due to nerve paralysis. Lagophthalmos is a condition where eyelid cannot close completely. If lagophthalmos was not soon detected and corrected, it could lead to corneal opacity and threat visual acuity (Grzybowski et al. 2015; Hogeweg 2001; Parikh et al. 2009; Lewallen et al. 2000; Lewallen & Courtright 2012). Leprosy patients with lagophthalmos usually have lesion somewhere in the facial area, and usually have disability also in their arms and legs when diagnosed with leprosy, compared to patients without lagophthalmos (Courtright et al 2002; Rathinam 2010; Lewallen & Courtright 2012). About 2-4% leprosy patients have lagophthalmos before diagnosed or during MDT (multi drug therapy) treatment, 6-10% were elderly patients and had disability (Hogeweg 2010). According to data in 2013-2015 in Dermatovenereology Polyclinic dr. Cipto Mangunkusumo Hospital, lagophthalmos was found in 2,4% of 501 new leprosy cases. All patients with lagophthalmos were MT type leprosy patients (Lasrindy 2016).

Lagophthalmos pathogenesis started when *M. leprae* invade peripheral nerve (Schwann cell) where there were protein bridging to Schwann cell cytoskeleton, which are laminin-2,  $\alpha$ -dystroglycan,  $\beta$ -dystroglycan, and dystrophin. *M. leprae* would enter Schwann cell endoneurium, and then stimulate inflammation response in nerve cells. Invaded nerve cells are facial cranial nerve (CN VII) zygomatic and temporal branches, which leads to orbicularis oculi muscle paralysis so that eyelid could not close completely (paralytic lagophthalmos), also ophthalmic branch of trigeminal cranial nerve (CN V) which leads to decrease in corneal sensibility. Paralytic lagophthalmos with decreased corneal sensibility could cause corneal opacity and decreased visual acuity that leads to blindness (Lewallen & Courtright 2012; Sjamsoe & Sjamsoe-Daili 2003; Grzybowski et al 2015; Ebenezer 2016).

Corneal opacity due to lagophthalmos was the most common cause of blindness in leprosy (Lewallen et al. 2000).

Lagophthalmos management depends on duration and size of lagophthalmos, also the presence of corneal exposure. In lagophthalmos with eyelid gap  $>6$  mm, presence of corneal exposure, and duration  $>6$  months, the ideal treatment is with eyelid reconstruction surgery (Hogeweg 2010). There were several reconstruction surgery techniques for lagophthalmos, although these techniques gave various results. The easiest surgery technique to manage lagophthalmos is permanent lateral tarsorrhaphy, which was done with joining upper and lower lateral side of the eyelid so that patient could still see from the central side. Even though, this technique has its limitation, which is limited temporal visual field and poor cosmetic result (Hogeweg 2001; Hogeweg 2010; Rajak et al. 2015).

Therefore, this study attempts to combine tarsorrhaphy technique with another eyelid reconstruction techniques, which are levator recess and canthopexy. Levator recess technique aims to weaken levator muscle to enable eyelid closure passively, while canthopexy aims to tighten lower eyelid, because in lagophthalmos due to orbicularis paralysis, there were tendency of lower lid laxity.

Another common technique to reconstruct CN VII paralysis as lagophthalmos management is upper eyelid loading, using gold weight implant (Rahman & Sadiq 2007). Gold weight implant has a high success rate as lagophthalmos treatment. This technique uses gold implant and attach it into the upper eyelid so that the weight of the gold pulled by the gravity and the eyelid closes passively when palpebral levator muscle relaxed. The advantages of this technique are: increasing eyelid closure with gravity pull, protecting cornea from exposure, and good cosmetic result. The disadvantages of gold weight implant technique are: expensive material, risk of complications, such as inflammation, allergic reaction, extrusion, migration, and astigmatism (Bladen et al 2012; Chi 2016). Wagh et al (2016) showed gold weight implant as the most effective treatment for paralytic lagophthalmos from keratopathy improvement and decrease in ocular surface defects.

Generally, eye disorders in leprosy patients were poorly diagnosed in primary health facility. Ocular manifestations in leprosy were assessed by general physician, dermatovenereology specialist, and ophthalmologist with different level of knowledge so that ocular complication in leprosy may still be underdiagnosed (Ebenezer 2016). Every eye disorders in leprosy patients, including lagophthalmos, need early detection and early treatment to prevent blindness. Eyelid reconstruction surgery is needed to correct paralytic lagophthalmos in leprosy patients, but not all health facility has a trained ophthalmologist to

do eyelid reconstruction surgery. Limited access and cost for treatment in tertiary health facility, leprosy patients commonly came when ocular complications have reached severe visual impairment. Therefore, this study is useful in ophthalmology field for several reasons:

1. There were no studies comparing effectivity and efficiency of various reconstruction surgery techniques for lagophthalmos in leprosy patients.
2. There were no complete data in Indonesia regarding incidence and prevalence of lagophthalmos due to leprosy.
3. With this research, better leprosy management can be carried out to prevent blindness from lagophthalmos in leprosy patients.

## **b. Objectives**

- Main objective

Comparing effectivity and efficiency between modified tarsorrhaphy and gold weight implant technique as operative treatment for paralytic lagophthalmos in leprosy patients

- Specific objectives

Assessing the success of modified tarsorrhaphy and gold weight implant techniques as reconstructive treatment for lagophthalmos in leprosy patients according to:

- a. Lagophthalmos distance pre- and post-operative
- b. Dry eyes assessments (subjective assessment with OSDI questionnaire and objective assessment with TBUT, Schirmer test without anesthesia and Schirmer test with anesthesia)
- c. Epitheliopathy
- d. Corneal exposure
- e. Corneal sensibility
- f. Complication intra-operative and post-operative, which are bleeding, infection, granulation, implant extrusion
- g. Duration of surgery
- h. Cost of surgery

### **c. Hypothesis**

Modified tarsorrhaphy is more effective and efficient than gold weight implant technique as operative treatment for paralytic lagophthalmos in leprosy patients.

### **d. Trial Design**

This study uses PROBE (Prospective Randomized Open-label Blinded-Endpoint) in which samples are randomized to allocate received intervention, principal investigator knows the intervention assigned according to randomization. Outcome measurements are carried out by three trained ophthalmologists as research team members, so that the measurements are done objectively and principal investigator is not biased.

## **2. METHODS**

### **a. Study Setting**

#### Target Population

Target population of this study are Paucibacillary (PB) or Multibacillary (MB) type leprosy patients with unilateral or bilateral lagophthalmos in Indonesia.

#### Study Population

Study population of this study are PB or MB type leprosy patients with unilateral or bilateral lagophthalmos who have completed MDT therapy in Jakarta, Makassar, or Tangerang.

#### Study Sample

Study population of this study are PB or MB type leprosy patients with unilateral or bilateral lagophthalmos who meet inclusion and exclusion criteria at Jakarta Eye Center Hospital (Jakarta), [name] Hospital (Makassar), or dr. Cipto Mangunkusumo Kirana Eye Hospital (Jakarta).

### **b. Eligibility Criteria**

#### Inclusion Criteria

1. PB or MB type leprosy patients with unilateral or bilateral lagophthalmos who have not done eyelid reconstruction surgery before
2. Age of 18 years old or older and able to have surgery with local anesthesia
3. Willing to take part as clinical trial subject and sign an informed consent

4.

#### Exclusion Criteria

1. Refuse to sign informed consent
2. History of eyelid reconstruction surgery
3. Patient with leprosy in acute stage (< 6 months) or in steroid therapy
4. Eyelid laxity > 8 mm

#### Drop Out Criteria

1. Patient who do not come for follow up appointments as assigned by research team members
2. Patient who withdrew during the study

#### **c. Interventions**

##### Modified Tarsorrhaphy Technique

1. Patient preparation and aseptic procedures on subject eye
2. Marking at eyelid crease skin
3. Subcutaneous anesthesia using Lidocain HCl 20 mg and Epinephrine 0.0125 mg/ml (Pehacain(R)) on upper eyelid and lateral side of the eye
4. Incision at skin crease and dissection of orbicularis muscle to clean superior tarsal border
5. Levator recess procedure with local anesthesia injection at conjunctiva to separate levator aponeurosis from conjunctiva. Open orbital septum at the level of superior tarsal. Excision of levator aponeurosis at its insertion site in the tarsal. Separate aponeurosis levator from conjunctiva as far as possible
6. Do canthotomy and lateral cantholysis. Excision of upper and lower eyelid margin as long as 10 mm from lateral canthal to central. Lateral tarsorrhaphy suture using polyglactin 6-0 with reverse cutting needle
7. Do canthopexy/lateral tarsal strip (LTS) using polyglactin 5-0 with reverse cutting needle and canthoplasty using polyglactin 6-0 with reverse cutting needle
8. Suture skin to form lid crease (skin-tarsal-skin) at 3 points and suture skin in between using polypropylene 6-0 with reverse cutting needle.

### Gold Weight Implant Technique

1. Patient preparation and aseptic procedures on subject eye
2. Marking at eyelid crease skin
3. Subcutaneous anesthesia using Lidocain HCl 20 mg and Epinephrine 0.0125 mg/ml (Pehacain(R)) on upper eyelid and lateral side of the eye
4. Incision at skin crease and dissection of orbicularis muscle to clean superior tarsal border
5. Open orbital septum at middle border of superior tarsal
6. Eversion of upper eyelid, do subconjunctiva anesthesia to separate aponeurosis from conjunctiva
7. Levator recess procedure with excision of levator aponeurosis at its insertion site in the tarsal. Separate aponeurosis levator from conjunctiva
8. Implant placed at superior tarsal border underneath levator recess with attachment to septal frill, and then fixed at tarsal using polypropilene 6-0 with reverse cutting needle.
9. Suture orbicularis muscle to cover implant using polyglactin 6-0 with reverse cutting needle and suture skinn using polypropilene 6-0 with reverse cutting needle.

### Intervention Monitoring

Researcher will monitor adverse events during and after surgery procedure. Any adverse events at any time during the study will be notified to the surgeon and will be treated by the surgeon or referred to related specialist.

### Concomitant Care and Interventions

All subjects should have completed MDT (multi drug therapy) treatment for leprosy and not in steroid treatment. Subject with previous ophthalmic surgery were excluded from the study. Patients with surgical complication from this study will be treated and will still be observed in this study.

#### **d. Outcomes**

##### **Effectivity Outcomes:**

##### **1. Lagophthalmos Distance**

Lagophthalmos distance is measured at central (middle pupil), nasal (medial limbus), and temporal (lateral limbus) between upper and lower eyelid while eyelids are closed without pressure and with gentle pressure. Distances are measured using caliper/ruler in millimeters.

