#### **f. Sample Size**

This study uses sample size calculation formula for two-tailed hypothesis test:

$$n = \frac{Sd^2 (Z_{1-\alpha/2} + Z_{1-\beta})^2}{(\mu_0 - \mu_a)^2}$$

$$n = 1,19^2 \frac{(1,96 + 0,842)^2}{1^2}$$
$$n = 12$$

n = total sample

Sd = standard deviation of mean difference (1.19)

$Z_{1-\alpha/2}$  = type 1 error (1.96)

$Z_{1-\beta}$  = type 2 error (0.842)

$\mu_0 - \mu_a$  = significant mean difference of both groups (1 mm represents significant)

Researcher determines sample size of minimum 12 eyes in each group.

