### Statistical Methods

Data will be analyzed using univariate, bivariate, and multivariate analysis. Univariate test is used to analyze frequency distribution of study variables. Bivariate test is used to analyze relation between two variables, using Independent T-Test, Wilcoxon, homogeneity test, and Mann-Whitney test. Multivariate test uses General Linear Model Repeated Measure with ANOVA. All tests using  $\alpha = 0.05$ .

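### No primary outcome is named, so neither the 5% error rate nor the 1 mm sample-size target attaches to a defined comparison

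*Protocol*

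**What the plan says.** **Objectives and hypothesis.** Section 1.b gives a main objective of comparing effectivity and efficiency, then eight specific objectives (a to h) without ranking. Section 1.c states: "Modified tarsorrhaphy is more effective and efficient than gold weight implant technique". No rule says which result, or how many, would establish either half.

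**Outcomes.** Section 2.d groups outcomes as effectivity and efficiency and calls none primary. The first is lagophthalmos distance: "Lagophthalmos distance is measured at central (middle pupil), nasal (medial limbus), and temporal (lateral limbus) between upper and lower eyelid". Each position is read without pressure and with gentle pressure.

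**Visits.** Section 2.e schedules the effectivity outcomes at 1 day, 7 days, 1 month, 3 months and 1 year, with no main visit.

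**Sample size.** Section 2.f says "This study uses sample size calculation formula for two-tailed hypothesis test" and defines the target only as "significant mean difference of both groups (1 mm represents significant".

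**Analysis.** Statistical Methods in section 3 lists two-group tests and a repeated-measures general linear model. On the level it says only "All tests using" α = 0.05.

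**The concern.** A two-sided 5% level limits false findings for one test fixed in advance. Here no test is fixed. Once the data are in, the position, pressure condition, visit or outcome that looks best could be put forward, and nothing in the protocol marks that as a departure from plan. The rate at which the trial would wrongly support its hypothesis is then unknown and above the nominal level.

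The sample size has the same gap. Variability and the meaning of 1 mm may differ between, say, the central gap without pressure at 1 year and the nasal gap with pressure at 7 days. Without a named target, a reader cannot judge whether 12 eyes per group suits the comparison that will carry the conclusion.

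**Working it through.** **1. The plan's own figure.** Inputs from section 2.f: "Sd = standard deviation of mean difference (1.19"), z values 1.96 and 0.842, difference 1 mm.

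n = 1.19² × (1.96 + 0.842)² / 1² = 1.4161 × 7.851 = 11.12, rounded up to 12.

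The stated 12 follows from the stated formula. (Whether a single-variance formula suits two groups is a separate matter.) What is missing is the outcome. The unit does not settle it: lagophthalmos distance, Schirmer wetting, corneal sensibility and corneal exposure are all recorded in millimetres.

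**2. Counting the measures (section 2.d).**
- Lagophthalmos distance: 3 positions × 2 pressure conditions = 6.
- Other effectivity measures: OSDI, TBUT, Schirmer with and without anesthesia, epitheliopathy, corneal sensibility, corneal exposure = 7.
- Efficiency: complications, duration, cost = 3.
- Total: 6 + 7 + 3 = 16 measures, of which 13 are effectivity.
- If each effectivity measure is tested at each of five visits: 13 × 5 + 3 = 68.

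The text does not say which count applies. A repeated-measures model can give one group test per outcome (16), while the listed two-group tests could be run visit by visit (68).

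**3. Chance of at least one false p<0.05, either direction.** For k independent tests this is 1 − 0.95^k. For a common correlation ρ between normal test statistics it is 1 − ∫ φ(u) [Φ((1.96 − √ρ u)/√(1−ρ)) − Φ((−1.96 − √ρ u)/√(1−ρ))]^k du, evaluated numerically. The correlations are assumptions; the protocol gives none.

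| Tests | Independent | ρ = 0.5 | ρ = 0.7 |
|---|---|---|---|
| 6 distances, one test each | 26% | 21% | 16% |
| 16 measures, one test each | 56% | 37% | 26% |
| 68 outcome-by-visit tests | 97% | 69% | 45% |

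Simulation of the same model agrees to about one percentage point.

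**4. Only false results that favour tarsorrhaphy.** Each two-sided 0.05 test errs in that direction with probability 0.025.
- Effectivity, 13 tests, independent: 1 − 0.975^13 = 28%. With a common correlation of 0.8: about 10%.
- Efficiency, 3 tests, independent: 1 − 0.975^3 = 7.3%.
- If one result on each side were enough, all nulls were true and the two sides independent: 0.280 × 0.073 = 2.1%.
- If the 65 effectivity tests (13 × 5) were run separately and were independent: 1 − 0.975^65 = 81%, and the joint figure is 0.807 × 0.073 = 5.9%.

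The joint figures need efficiency to be truly null as well. The Introduction lists expensive material as a disadvantage of the gold implant, so a real cost difference in favour of tarsorrhaphy is expected. The error of the joint claim then falls back towards that of the effectivity half: about 10-28% with one test per measure, against 2.5% for a single named primary.

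**The case against.** **The repeated-measures model.** The protocol never says that each outcome is tested separately at each visit, and its model can cover all visits in one test. This stands: 68 is an upper bound, and 16 is the fair lower count. Even one test per measure leaves the chance of a false result in either direction well above 5%.

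**Multiplicity belongs in the SAP.** A missing adjustment procedure can be left to a plan that is not shown, and is not criticised here. The target of the sample-size calculation cannot be left there, because the protocol makes that calculation. Nor is the protocol silent on the level: it sets one α for every test.

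**Lagophthalmos distance is the implied primary.** It comes first in the list and fits a 1 mm target. This is plausible, but it still leaves six readings and five visits open.

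**Two stronger readings go too far.** A reader might infer that a false claim for tarsorrhaphy is likely by chance. The 56% and 97% figures count results in either direction under independence. The protocol also does not say that one significant result suffices, and its hypothesis requires both effectiveness and efficiency.

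A reader might also infer that the temporal reading is biased by construction, because the tarsorrhaphy steps include "Excision of upper and lower eyelid margin as long as 10 mm from lateral canthal to central". The documents give no anatomical dimensions that place the lateral limbus inside that segment. A gap made smaller by surgical closure would in any case be a real effect of the operation, not a chance error. At most, the temporal reading lies close to the sutured segment, which is a reason to prefer the central one.

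**Conclusion.** The point holds in a limited form. No primary outcome, position, pressure condition or visit is named, the 1 mm target identifies no comparison, and 0.05 applies to every test, so the family-wise error for the hypothesis is uncontrolled. With one test per measure, the chance of some false p<0.05 in either direction is 26% (six distances) or 56% (16 measures) if independent, and about 16-21% or 26-37% at correlations of 0.7 to 0.5. The 97% figure needs 68 separate, independent tests. For false effectivity results favouring tarsorrhaphy, about 10-28% is the relevant range. These sizes rest on assumed correlations and on one significant result being treated as enough, which the protocol neither states nor rules out. The absence of a named primary depends on neither assumption. This is a cheap improvement that belongs in the protocol.

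**What to change.** In section 2.d, name one primary comparison, for example central lagophthalmos distance without pressure at 1 year, compared between arms at two-sided 0.05. One pre-specified group contrast from the repeated-measures model would serve equally well. The choice is the sponsor's; what matters is that outcome, position, pressure condition and visit (or contrast) are fixed.

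In section 2.f, state that the 1 mm difference and the standard deviation refer to that comparison.

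Make all other positions, conditions, visits and outcomes secondary, reported with estimates and 95% confidence intervals. Allow no superiority claim from them alone, or adjust them by Holm's method. Restrict the sentence on α in Statistical Methods to match.

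The cost is protocol wording. The sponsor gives up claims that rest on isolated secondary results; no extra eyes, visits or measurements are needed.
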